# Corticosteroid injection plus exercise versus exercise, beyond advice and a heel cup for patients with plantar fasciopathy: protocol for a randomised clinical superiority trial (the FIX-Heel trial)

**DOI:** 10.1186/s13063-019-3977-0

**Published:** 2020-01-02

**Keywords:** Plantar fasciopathy, Heavy-slow resistance training, Corticosteroid injection, Foot orthoses, Patient advice

## Abstract

**Background:**

Plantar fasciopathy has a lifetime prevalence of 10%. Patients experience sharp pain under the heel, often for several months or years. Multiple treatments are available, but no single treatment appears superior to the others. A corticosteroid injection offers short-term pain relief but is no better than placebo in the longer term (> 8 weeks). Heavy-slow resistance training has shown potentially positive effects on long-term outcomes (> 3 months), and combining exercises with an injection may prove to be superior to exercises alone. However, the effect of heavy-slow resistance training compared with a simpler approach of patient advice (e.g., load management) and insoles is currently unknown. This trial compares the efficacy of patient advice with patient advice plus heavy-slow resistance training and with patient advice plus heavy-slow resistance training plus a corticosteroid injection in improving the Foot Health Status Questionnaire pain score after 12 weeks in patients with plantar fasciopathy.

**Methods:**

In this randomised superiority trial, we will recruit 180 patients with ultrasound-confirmed plantar fasciopathy and randomly allocate them to one of three groups: (1) patient advice and an insole (*n* = 60); (2) patient advice, an insole, and self-dosed heavy-slow resistance training consisting of heel raises (*n* = 60); or (3) patient advice, an insole, heavy-slow resistance training, and an ultrasound-guided corticosteroid injection (*n* = 60). All participants will be followed for 1 year, with the 12-week follow-up considered the primary endpoint. The primary outcome is the Foot Health Status questionnaire pain domain score. Secondary outcomes include the remaining three domains of the Foot Health Status Questionnaire, a 7-point Global Rating of Change, the Pain Self-Efficacy Questionnaire, physical activity level, health-related quality of life measured by the EQ-5D-5L, and Patient Acceptable Symptom State, which is the point at which participants feel no further need for treatment. Additionally, a health economic evaluation of the treatments will be carried out.

**Discussion:**

This trial will test if adding heavy-slow resistance training to fundamental patient advice and an insole improves outcomes and if a corticosteroid injection adds even further to that effect in patients with plantar fasciopathy.

**Trial registration:**

ClinicalTrials.gov, NCT03804008. Prospectively registered on January 15, 2019.

## Background

One in ten persons will develop plantar fasciopathy (PF) [1, 2]. The condition accounts for 8% of all running-related injuries but is also common in the general population [3–5]. A high running volume is associated with a higher risk of developing PF, and despite a lack of prospective studies to identify risk factors among non-runners, a high body mass index is thought to be a risk factor [6]. Pain is often worse during the first steps after getting out of bed or during the first steps after periods of non-weight-bearing [7].

PF was formerly known as ‘plantar fasciitis’ or ‘heel spur syndrome’ and has historically been considered a self-limiting condition in which 80% are expected to achieve symptom-free status within 12 months. This view of a self-limiting condition has been challenged by research [1, 8–11]. Approximately half of patients referred to a specialised secondary care clinic still experienced pain 10 years after treatment [9], and 40% of patients in a randomised controlled trial still had symptoms 2 years after plantar fascia-specific stretching and wearing insoles [8]. Patients with PF show greater levels of depression, stress, anxiety and kinesiophobia and experience limitations in both mobility and health-related quality of life compared with pain-free individuals [12–14]. Moreover, PF may be associated with several days of sick leave. Davis et al. found that 6 of 105 patients had taken as much as 3 months off work [15], and we recently found that 23% of patients in the workforce had taken a median of 30 days off work due to their heel pain in one study [16] and 20% had taken between 5 and 548 days off work in another [17]. Thus, the consequences for both patients and society are marked.

A systematic review and network meta-analysis compared several commonly used treatment options for PF [18]. Overall, they concluded that none of the investigated treatments were superior to the others, but different treatments may have different temporal profiles. Some are efficacious in the short term (< 4 weeks), such as an injection with corticosteroid, whereas others (e.g., exercises or orthoses are more efficacious in the longer term [> 12 weeks]) [18–22]. Heavy-slow resistance training (HSR) was not included in the review, but it is generally known for a long-term efficacy in the rehabilitation of both upper- and lower-limb tendinopathies [23–25]. In PF, HSR has been found to be superior to plantar fascia-specific stretching, but only 6% achieve an acceptable symptom state within 12 weeks [16, 26]. This emphasises the need for additional improvements to current care of these patients.

Combining HSR with a corticosteroid injection may provide both short- and long-term pain relief for individuals with PF. We recently conducted a feasibility study of the combination of these two treatments, which supports running an efficacy trial. Patients’ rating of acceptability, time to commencement of exercise after the injection, compliance with exercise, recruitment rate, and changes in foot-related health and function over time supported this current proposed trial [27]. In theory, combined treatments could supplement each other and give both an immediate and long-term pain reduction.

Repeated corticosteroid injections and a combination of stretching and foot-strengthening exercises have been investigated before, but the combination of HSR and a single corticosteroid injection is yet to be studied [28]. Previous studies in other tendinopathies only compared the combined treatments with one of the treatments and reported no differences [24, 29]. The limitation of these studies is that it remains unknown if any of the treatments have had some effect or no effect overall on the condition, because the trials did not include a control arm [24, 29]. We propose that a trial of combined interventions versus one of the interventions requires a control arm. A minimal intervention (control arm) consisting of patient advice, which reflects current general practitioner (GP) practice (unpublished data), will enable a meaningful comparison with more time-consuming and expensive treatments, such as exercises and injections. If we do not fill this knowledge gap, we might use costly and time-consuming treatments without knowing the effect compared with simpler treatment. To our knowledge, there is no literature available on the cost-effectiveness of alternative treatments of PF [30]. Despite treatment costs for PF possibly seeming relatively small compared with other more expensive health technologies, the productivity costs to society may be substantial in PF due to patients’ sick leave.

The present trial is the product of a series of preceding studies conducted by our group in this patient population in general practice. Interviews with GPs about the management of PF showed a high heterogeneity wherein some would give a steroid injection at first consultation, some would prescribe exercises, and some would refer to a physiotherapist (unpublished data). However, commonalities were to give patients advice on what they could do to self-manage and an uncertainty about the effectiveness of the many treatments available for PF. To investigate if we could improve outcomes associated with HSR, we compared a traditional pre-determined HSR programme with a self-dosed programme to target self-efficacy and increase the exercise dose received. We found that both programmes were associated with similar improvements [16]. Following that randomised trial, we investigated the feasibility of combining HSR with an ultrasound-guided corticosteroid injection in the feasibility study described above as a final step before initiating the present trial [27].

### Objectives

The purpose of this trial is to investigate the efficacy of fundamental patient advice and a heel cup (PA) versus fundamental patient advice and a heel cup plus heavy-slow resistance training (PAX) versus a combination of fundamental patient advice and a heel cup plus heavy-slow resistance training and an ultrasound-guided corticosteroid injection (PAXI) in improving the Foot Health Status Questionnaire pain domain score after 12 weeks in individuals with PF.

#### Hypotheses

Hypothesis 1: The group receiving PAXI will be superior to the group receiving PAX.

Hypothesis 2: The group receiving PAXI will be superior to the group receiving PA only.

Hypothesis 3: The group receiving PAX will be superior to the group receiving PA only.

## Methods

### Design and setting

The FIX-Heel Trial is designed as a randomised superiority trial with a three-group parallel design. Reporting of the protocol follows the Standard Protocol Items: Recommendations for Interventional Trials (SPIRIT) statement (checklist uploaded as Additional file 1), TiDieR (Template for Intervention Description and Replication checklist and guide) and the Consensus on Exercise Reporting Template for intervention description [31–33]. The preparation of the trial, including publishing this trial protocol, was done in accordance with the PREPARE trial guide [34]. Before the inclusion of the first participant, the trial was registered with ClinicalTrials.gov (NCT03804008). Patients will be recruited from general practice and via social media (see below). However, for pragmatic reasons, the information and training instructions will be given at the physiotherapy department at Aalborg University Hospital, and injections will be given at a private rheumatology clinic (ReumaNord) situated in Aalborg, Denmark. Participants will attend the baseline and 12-week follow-up appointments at the hospital, whereas a link to the questionnaires used will be sent via REDCap (Vanderbilt University, Nashville, TN, USA) to participants’ e-mail addresses for the 4-week, 26-week and 52-week follow-ups.

### Roles and responsibilities

The project manager is a physiotherapist with 8 years of experience in treating patients with musculoskeletal conditions. He will be responsible for recruitment and analysing data whilst blinded to group allocation. Two physiotherapists working at the Aalborg University Hospital with 5 and 6 years of experience, respectively, were recruited and will be responsible for eligibility screening, delivering interventions and being in contact with participants throughout the trial. Before the inclusion of the first participant, the physiotherapists had received 10 and 19 h of training, respectively, in the procedures of the trial by the project manager. This includes putting four pilot study participants through all aspects of the trial processes. The ultrasound-guided injection will be performed by a rheumatologist who has more than 15 years of experience with performing ultrasound-guided injections.

### The adaptive recruitment strategy

Participants will primarily be recruited from general practice, but to ensure that the trial timeline is maintained, we will include participants through social media (Facebook). Initially, we aim to recruit from ten general practices in the North Denmark Region. We will reach out to the practices using an open invitation in which we ask for practices interested in being part of trial recruitment through the Facebook page of the Center for General Practice at Aalborg University and through our network of GPs in the North Denmark Region. If this is not sufficient, the project manager will contact general practices directly. The GPs are offered a 30-min presentation about PF and the trial at their own practice. If recruitment from general practice is inadequate, we may employ one of the practices’ secretaries, who examines the GPs’ daily plans for potential trial participants. The secretary will then remind the GP of informing the patient about the trial if the patient is potentially eligible for inclusion.

General practices will receive an honorarium per patient they refer to the project manager. It is a standard honorarium stipulated by the Danish Committee of Multipractice Studies in General Practice (approximately €18). Before they agree to participate in recruitment, they will be informed that they are expected to refer a minimum of two patients per month. On the basis of the number of referrals we receive, we will categorise general practices into three symbolic zones: green, yellow and red. Practices in the green zone will have referred a minimum of two patients during the past month; practices in the yellow zone will only have referred one patient during the past month; and practices categorised in the red zone will have failed to refer any patients during the past month or they will have been in the yellow zone for two consecutive months. Practices in the red zone will be contacted by the project manager to discuss whether other strategies are needed to increase referrals or if the reason for the lack of referrals is a lack of potentially eligible participants presenting at the practice. If half of the clinics are categorised in the red zone or if less than half of the referred patients are not eligible during a 2-month period, we will recruit additional general practices.

Recruitment through Facebook will be used if fewer than ten participants have been included during any given month following referrals from general practices. We will post information about the trial on a Facebook page called ‘Treatment of pains under the foot’ and use the sponsoring function. We target the sponsoring towards both males and females aged 18 years or older who are living within an 80-km radius of Aalborg, Denmark. Each sponsorship will last for 1 week. If this is not sufficient to achieve at least ten included participants per month, including those referred from general practices, we will increase the amount of money per sponsorship first and increase the radius second. Both strategies will increase the reach of the sponsorship. We are able to calculate the cost of each included participant recruited via Facebook by dividing the cost of 1 week of sponsoring by the number of participants included following that week. We have done this before in two studies to compare the cost of participants from general practice with participants from Facebook, and participants recruited from Facebook cost approximately half that of those from general practice [16, 27].

GPs will invite patients to be included in the trial during their normal consultations with patients with pain under the heel. The general practices will send the contact information of patients to the project manager, whereas potential participants recruited through Facebook will contact the project manager directly. The project manager will then inform the physiotherapists about the potential participant, whom they will contact to perform an eligibility telephone screening. The project manager will have no contact with participants after he has forwarded the contact details to the physiotherapists.

### Eligibility criteria

The inclusion criteria are as follows: history of inferior heel pain for at least 3 months before enrolment, pain on palpation of the medial calcaneal tubercle or the proximal plantar fascia, thickness of the plantar fascia ≥ 4.0 mm, and mean heel pain of ≥ 30 mm on a 100-mm visual analogue scale (VAS) during the previous week. The exclusion criteria are as follows: younger than 18 years of age; diabetes; history of inflammatory systemic diseases (e.g., rheumatoid arthritis or spondyloarthritis) [19]; prior heel surgery; pregnancy or breastfeeding; corticosteroid injection specifically for PF within the previous 6 months; pain or stiffness in the first metatarsophalangeal joint to an extent that the exercises cannot be performed; known hypersensitivity to corticosteroids or local anaesthetics; skin or soft tissue infection near the injection site; receipt of any treatment by a healthcare professional for PF within the previous 12 weeks; or made any substantial changes to usual self-care of the condition in the last 4 weeks (e.g., started using insoles, started performing stretching, made a substantial decrease in physical activity level). These criteria are in line with those of similar studies in this patient population [16, 17, 19]. These criteria lead to a representative sample of patients with PF because previous studies include the majority of potentially eligible participants [16, 17, 19].

### Randomisation and blinding

Participants will be stratified by sex and block-randomised in random concealed block sizes of 3 to 12 (1:1:1) in three parallel groups. A researcher not involved in the trial generated the allocation sequence using a random number generator on www.sealedenvelope.com and is the only person who knows the block sizes. The researcher was trained by the project manager in generating allocation sequences, and the process was piloted.

The randomisation is coded so that the project manager does not know which intervention is linked to which group number (group 1, 2 or 3). The envelopes will be kept in a locked room at Aalborg University Hospital where only the two physiotherapists involved in baseline testing have access. The randomisation schedule was prepared at the Center for General Practice at Aalborg University by a person not involved in the actual trial. The notes in the envelopes state both group number and intervention, and the physiotherapists responsible for assessing participants and delivering the interventions will not be aware of the coding before they open the first envelopes. In practice, after a participant has been enrolled, has filled out questionnaires, and has received initial patient advice and information regarding the practicalities of participation, the physiotherapist will take an envelope and assign the participant to the allocated treatment on the basis of randomisation.

The project manager will be responsible for performing the statistical analyses and will remain blinded to the coding until after the analyses have been performed. The analyses will be performed after the examination that includes the primary endpoint (the 12-week follow-up) of the last participant.

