### Patient and end-user involvement

To involve both patients and end users in designing the intervention, the participant leaflet was developed on the basis of semi-structured interviews with five patients with PF and five GPs. Patients were asked to describe their heel pain, how it had affected them and which topics they felt would be important to include in a leaflet and in advice to a patient in general. GPs were asked about their experience with the patient group, which treatments they would consider and which topics they felt would be important to include in a leaflet and in advice to the patient in general. The leaflet and fundamental patient advice that the physiotherapists will deliver orally to patients are a triangulation of the results of the interviews with both patients and GPs and recommendations from clinical guidelines and a systematic review [1, 6, 51].

We will invite representative participants from each group to be part of the future interpretation of the results. Their interpretation will be part of the dissemination of the results in the trial report and during conferences. In practice, we will invite two randomly selected participants of each group after the primary outcome has been collected. If a participant declines, we will randomly select a new participant from the same group.

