### Statistical analyses

All statistical analyses will be performed by a blinded data analyst according to a pre-established analysis plan using the intention-to-treat principle. This plan is written in consultation with a statistician and will be published on the Aalborg University website before the inclusion of the last participant. SPSS software (IBM Corporation, Armonk, NY, USA) will be used as statistical software. We will use Q-Q plots and histograms to assess data normality. Missing outcome data will be imputed using multiple imputations based on the values from previous follow-ups, sex, age, and group allocation.

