#### Primary analysis

The primary analysis will investigate the between-group difference in FHSQ pain. We will use a linear mixed effects model with the participant as a random effect, and time (4, 12, 26 and 52 weeks), group allocation (PA or PAX or PAXI) and baseline value as fixed effects. Conclusions will only be drawn on the basis of the primary endpoint (12 weeks).

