#### Secondary analyses

We will also analyse the mean values of the secondary continuous outcomes (other domains of FHSQ, PSEQ and physical activity level) using linear mixed models. The risk difference ($$ =\frac{Positive\ outcomes\ in\  one\  group}{Number\ of\ participants\ in\ group} $$ - $$ \frac{Positive\ outcomes\ in\ another\ group}{Number\ of\ participants\ in\ group} $$) will be calculated for the dichotomised GROC to determine the probability of being improved, for the PASS (yes/no) to determine the probability of achieving a self-evaluated satisfactory result within the 12, 26 and 52 weeks of intervention. We will also calculate risk differences to determine the probability of experiencing a deterioration of PF, defined as a decrease in FHSQ pain ≥ 14.1 points from one follow-up to another or changing one’s status from having achieved PASS to no longer having achieved PASS. We will calculate the number needed to treat for the primary outcome at the primary endpoint as 1/risk difference. We will use a Kaplan-Meier survival analysis and compare survival curves using log-rank tests to investigate between-group differences in time to achieving PASS [55, 56]. If a participant changes PASS multiple times (e.g., achieving PASS before 12 weeks, reporting not to have achieved PASS at 26 weeks and then having achieved PASS again at the 52-week follow-up), only time to the first PASS achieved is used in the analysis.

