### Strengths

First, the involvement of patients and GPs in developing the patient advice intervention enables a high level of acceptability for users. Second, all of the interventions are within scope, knowledge and skill levels of primary care clinicians and practices, so they will have a high feasibility of being implemented, regardless of trial findings. Third, all potential outcomes of the trial may influence future clinical practice. If no superiority of one intervention is found over the others, the minimally invasive or the most cost-effective should be implemented, depending on patient preferences. Fourth, to minimise bias, the data analysis will occur blind to group allocation and will be performed according to a pre-established and publicly accessible analysis plan.

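### The stated time of analysis does not secure the analyst blinding claimed for the 26-week, 52-week and cost-utility results, and the patient panel may be drawn before follow-up ends

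*Protocol article*

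**What the plan says.** Under Randomisation and blinding, the project manager is the analyst. He "will remain blinded to the coding until after the analyses have been performed", and the next sentence gives the time: "The analyses will be performed after the examination that includes the primary endpoint (the 12-week follow-up) of the last participant". No second step is given for data that arrive later.

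The blinding claim is wider than that. Statistical analyses states: "All statistical analyses will be performed by a blinded data analyst". Strengths lists among the safeguards against bias that "the data analysis will occur blind to group allocation".

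Several planned results need later data:

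- The primary model has "time (4, 12, 26 and 52 weeks), group allocation (PA or PAX or PAXI) and baseline value as fixed effects".
- Secondary analyses estimates the probability of reaching PASS "within the 12, 26 and 52 weeks of intervention", along with time to PASS and deterioration between follow-ups.
- Cost-effectiveness outcomes sets a 1-year horizon for QALYs.

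Design and setting has the 26- and 52-week questionnaires completed through an e-mailed link.

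On the patient panel, Patient and end-user involvement says: "we will invite two randomly selected participants of each group after the primary outcome has been collected". Their task is to help interpret the results. Nothing requires that they have completed follow-up.

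**The concern.** The rule for when blinding ends and the claim of what is blinded do not match. Only one analyst is named. If he learns the group key once the 12-week results are out, he would run the 26- and 52-week analyses knowing the allocation. The same holds for the cost-utility analysis if it falls to him; the article names no one else. Under Data monitoring and quality assurance he also checks the data weekly, and he would then do so with the key while forms are still arriving.

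Participants know their treatment and report the later outcomes themselves, so a blinded analyst is one of the main protections left for those time points. The panel raises a second, smaller risk. A participant who learns which arm did better and then completes the 52-week FHSQ, PASS, GROC or EQ-5D-5L may answer differently.

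**Working it through.** The plan gives no figure of its own on this point, so the check sets the statements side by side and then works out the calendar.

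**1. Two readings of the blinding rule.**

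- *The analyses are those run after the last 12-week visit.* The stated time is then right, but blinding ends before the later analyses, and the claim that all analyses are blinded is not secured.
- *The analyses are all planned analyses.* The blinding claim then holds, but the stated time is too early. The last 52-week form is due 52 − 12 = 40 weeks after the last 12-week visit.

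On either reading, Randomisation and blinding has to be reconciled with Statistical analyses and Strengths.

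**2. Inputs (Trial status, Sample size).** First inclusion was on 7 February 2019; 96 participants were included by 5 October 2019; recruitment is expected to end in July 2020; the target is 180.

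**3. Assumptions.** Accrual is even within each period, the last inclusion falls on 1 or 31 July 2020, and drop-out is ignored. The first period has 96 inclusions in 240 days, or 0.4 per day. The second has 84 inclusions in 270 days (to 1 July) or 300 days (to 31 July).

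**4. Participants still owing forms at the last 12-week visit.** A participant owes the 52-week form if included less than 52 weeks before that visit, and the 26-week form if included less than 26 weeks before it.

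| | Last inclusion 1 July 2020 | Last inclusion 31 July 2020 |
|---|---|---|
| Last 12-week visit | 23 September 2020 | 23 October 2020 |
| Cut-off for week 52 | 25 September 2019 | 25 October 2019 |
| Included by then | 0.4 × 230 = 92 | 96 + 84 × 20/300 = 101.6 |
| Owe week 52 | 180 − 92 = 88 (48.9%) | 180 − 101.6 = 78.4 (43.6%) |
| Cut-off for week 26 | 25 March 2020 | 24 April 2020 |
| Included by then | 96 + 84 × 172/270 = 149.5 | 96 + 84 × 202/300 = 152.6 |
| Owe week 26 | 30.5 (16.9%) | 27.4 (15.2%) |
| Last 52-week form due | 30 June 2021 | 30 July 2021 |

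In the first column the week-52 cut-off falls before 5 October 2019. All 84 later inclusions (84/180 = 47%) would therefore be pending whatever the accrual pattern after that date.

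**5. The panel.** Two are drawn from 60 in each group. With pending participants spread evenly over groups, 29 or 26 per group are pending.

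- Expected number of the six still owing week 52: 6 × 29/60 = 2.9, or 6 × 26/60 = 2.6.
- Chance that at least one does: 1 − [C(31,2)/C(60,2)]³ = 1 − (465/1770)³ = 0.98, or 1 − [C(34,2)/C(60,2)]³ = 1 − (561/1770)³ = 0.97.

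**6. Scale of a panel effect.** If one panel member in an arm of 60 shifted by a full 14.1 points, which is the difference used for the sample size, the arm mean would move by 14.1/60 = 0.24 points. Two such members would move it by 0.47.

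**The case against.** A reader might infer that the 26- and 52-week analyses cannot be blinded. The article does not say so. It gives only an earliest time for the analyses, and no section states that the key is opened at that time. The primary model itself includes weeks 26 and 52, which favours the reading that the key stays closed until everything is done. A colleague without the key could also run the later work. This stands against the word cannot. It does not remove the conflict, because on that reading the stated time of analysis is wrong, and no second analyst is named.

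A reader might also infer that some participants see results before their last self-report. The article dates the invitation and not any sharing of results, and at most six of 180 are involved. The 97% to 98% chance in step 5 says only that at least one invited person would still be in follow-up. It does not measure bias, and step 6 shows how little one person can move an arm mean.

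There are real safeguards. The analysis plan is written with a statistician and is to be published before the last inclusion, hence at least 12 weeks before the earliest possible opening of the key. That limits the analyst's discretion, though it does not fix every data-handling and programming decision. He also has no contact with participants after forwarding their details. Primary analysis confines conclusions to 12 weeks, and all 12-week questionnaire data are in hand before any opening of the key.

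Finally, the full protocol and the analysis plan are not shown and may settle the sequence. A missing code-break procedure would be no finding. This point rests on statements in the article that do not fit together.

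**Conclusion.** The point holds as a failure to secure what is claimed, and not as proof that later analyses will be unblinded. On the natural reading, the rule protects the 12-week analyses only, while the claim covers all of them. The later analyses would follow a possible opening of the key at which 44% to 49% of participants still owe the 52-week form and 15% to 17% the 26-week form. If the panel were drawn and shown results then, 2.6 to 2.9 of its six members would be expected still to owe their last self-report.

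These figures rest on even accrual, a last inclusion in July 2020 as forecast, no drop-out, and an invitation made at the earliest date allowed. The risk is small and touches the secondary and economic results only. The 12-week data and the conclusions drawn from them are unaffected.

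**What to change.** Reconcile Randomisation and blinding with Statistical analyses and Strengths by stating when the group key is opened relative to each set of results. Either of these would do:

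- Keep the key sealed until the 26-week, 52-week and cost-utility analyses are final.
- If 12-week results are to be released earlier, freeze and date the programs for all later analyses before opening the key, or have a colleague who has not seen the key run them.

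In Patient and end-user involvement, add that the panel is drawn only from participants who have returned the 52-week form.

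The change is one of wording, and the sample size stays as it is. The first option opens the key about 40 weeks later, around 30 June to 30 July 2021 instead of 23 September to 23 October 2020. The second requires the later programs to be written early. A panel that meets before all follow-up has ended would consist of earlier recruits.
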